**Fig. 5 Fig5:**
[figure not shown]
Study flow diagram. Randomization before T0. Five study visits every 3 months for 12-month study duration. Qualitative data collection with a representative subsample of study participants

### Outcomes

#### Baseline parameters

At baseline (T0), sociodemographic data (age, sex, nationality and language, educational background, family and occupation status) and history of illness (ICD-10 diagnoses, duration of illness, number of previous hospitalizations, previously prescribed medications, substance abuse) is collected via patient and clinician-rated questionnaires (Table 1).

**Table 1 Tab1:** Planned timepoints and data collection

Scale/item	Visit 0 (T0)	Visit 1 (T3)	Visit 2 (T6)	Visit 3 (T9)	Visit 4 (T12)
	Baseline	Week 13 +/- 3 weeks	Week 26 +/- 3 weeks	Week 39 +/- 3 weeks	Week 52 +/- 3 weeks
Written informed consent^a^	X^b^				
Screening/Assessment of inclusion/exclusion criteria^c^	✓^d^				
Sociodemographic characteristics	X				
Psychiatric diagnose(s) after ICD plus code	✓				
Change of psychiatric diagnosis(es)		✓	✓	✓	✓
Duration since first diagnosis	✓				
Number of previous episodes until now	✓				
Psychiatric comorbidities	✓				
Number of hospitalizations until now	✓				
Hospitalization days due to psychiatric illness in the past two years	✓				
Substance abuse	X	X	X	X	X
Alcohol abuse	X				
Smoking	X				
Currently psychiatric medication(s)	✓	✓	✓	✓	✓
Change and date in psychiatric medication(s)		✓	✓	✓	✓
Current other measures: e.g., psychotherapy, group therapy	✓	✓	✓	✓	✓
Rehospitalization (yes/no) and brief summary of admission reasons		✓	✓	✓	✓
Days in hospital since last study visit		✓	✓	✓	✓
Time to hospitalization		✓	✓	✓	✓
eHeals-g	X				
Questionnaire on prospective acceptance of eHealth	X and ✓				
Alarms since last study visit		✓	✓	✓	✓
Measures taken, if any, following the alarm		✓	✓	✓	✓
EWSQ-10P (control group only)	X	X	X	X	X
SDMQ-9	X	X	X	X	X
PAM13	X	X	X	X	X
ZUF-8	X	X	X	X	X
15-STARS	X	X	X	X	X
Question on Adherence	X	X	X	X	X
CGI-S/C	✓	✓	✓	✓	✓
PANSS-6	✓	✓	✓	✓	✓
FORSE	X	X	X	X	X
EuroHisQoL	X	X	X	X	X
WHODAS 2.0	X		X		X
SOFAS	✓	✓	✓	✓	✓
ANTISIDES	X				X
UKU-SERS self-rating	X				X
Mannheimer Resource Consumption Module	X				X
Reason for Dropout^e, f^ (if applicable)		✓	✓	✓	✓

^a^Written informed consent must be obtained at Baseline Visit 0 before data collection starts

^b^A X indicates the scale is patient-rated

^c^Screening can be done at Visit − 1 before Baseline or on the same day of Baseline at Visit 0

^d^A ✓ indicates the scale is clinician-rated

^e^Reasons for drop-out: Ineffectiveness of treatment, deterioration of condition, medication side effects, non-compliance, patient withdrawal of consent, lost-to-follow-up, additional adverse event, others

^f^In case of a drop-out, an early-termination visit should be conducted like the planned end-of-study visit (Visit 4, week 52). For qualitative interviews, the same procedure applies

To assess relevant factors contributing to the adherence to the digital intervention and its efficacy, we ask patients and clinicians about their acceptance of digital health interventions [34]. Patients additionally provide answers to the German version of the eHeals questionnaires (eHeals-g) on health-related Internet use [35].

#### Primary outcome

As the primary outcome we evaluate whether the 12-month intervention phase, during which the intervention group utilizes a smartphone-based relapse monitoring app that monitors early warning signs in addition to treatment as usual (TAU), reduces the number of patients readmitted to the hospital due to psychiatric reasons at least once during the study period. Hospitalization is defined as an increased level of care, including an inpatient stay of at least one day, a day patient stay, or home treatment due to exacerbation of psychiatric symptoms (not social reasons). Therefore, hospitalizations (if applicable) are assessed at every study visit, i.e., every three months, following the baseline assessment (T0).

#### Secondary outcomes

To complement our primary outcome of hospitalizations, we assess whether the intervention reduces the days spent in hospital and the time to hospitalization at three month-interval study visits (T0, T3, T6, T9, T12).

At every study visit (T0 – T12) we assess whether the app promotes more shared decision-making in the course of treatment (Shared Decision Making Questionnaire, SDM-Q9) [36], changes fear of relapse (Fear of Recurrence Scale Questionnaire, FORSE) [15], increases patient satisfaction (Patient Satisfaction Questionnaire, ZUF-8) [37] and patient activation (Patient Activation Measure, PAM-13) [38], and thus potentially improving medication adherence (Screening Tool for AdheRence to medicineS, 15-STARS) [39].

To better understand whether the intervention improves symptomatology, we use the 6-item version of the Positive and Negative Syndrome Scale (PANSS-6) [40] and the Clinical Global Impression Severity/Improvement (CGI-S/C) [41]. All three scales are rated by the clinician after patient study visit (T0 – T12). The clinician-rated Social and Occupational Functioning Assessment Scale (SOFAS) [42] is also assessed at the same timepoints.

Changes in Quality of Live (QoL) are assessed via the patient-rated EUROHIS-QOL [43] every three months. Patients report changes in social/global functioning via the WHODAS 12-item scale [44] at T0, T6 and T12. We evaluate the presence and severity of medication side effects using the Udvalg for kliniske undersøgelser scale (UKU-SERS) [45] and patient-reported antipsychotic and antidepressant side-effect scale (ANTISIDES). Those two measures are assessed at baseline (T0) and after study completion (T12).

To evaluate whether the implementation of a smartphone-based relapse monitoring smartphone is cost-effective from a pharma-economical perspective, we use the Mannheimer Resource Consumption Module Questionnaire at T0 and T12 [46].

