## Methods

### Trial design

The planned study (“IT-based relapse monitoring for schizophrenia”; acronym: ILIA) is a randomized-controlled (RCT), multicenter clinical trial evaluating the use of a smartphone- and web-based monitoring system for early warning signs of relapse integrated into standard clinical treatment, compared to treatment as usual (TAU) without digital monitoring. The study is conducted in outpatients with schizophrenia or schizoaffective disorders at 8 psychiatric hospitals in Munich, Augsburg and Berlin (Klinikum rechts der Isar, Ludwig-Maximilians-Universität (LMU) Klinikum, Isar-Amper-Klinikum München-Schwabing, München-Ost, Atriumhaus and Fürstenfeldbruck, Bezirkskrankenhaus Augsburg, Charité Universitätsmedizin Berlin). The inclusion is already possible at the end of an inpatient stay. The RCT is planned for 24 months, with the patients being recruited sequentially for 12 months. The intervention duration itself is 12 months. The protocol is registered in the German Clinical Trials Register (ID: DRKS00034991; registration date: 30.08.2024). An independent ethics committee reviewed and approved the research project (Technical University Munich, approval number: 2024-242-S-KK). The respective ethics committees of the participating clinics have followed the lead opinion of the ethics committee of the Technical University of Munich.

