**Fig. 1 Fig1:**
[figure not shown]
Interface of the Sigma.me App

Graphical depictions of weather icons within the smartphone app represent participants´ current health status based on questionnaire responses (Figs. 1 and 2). The various icons and their meanings are as follows: The smiling sun indicates no deterioration based on the questionnaire responses, suggesting that the patient is stable. The sun with a few clouds reflects a slight deterioration, but not enough to trigger an alarm period. The rain cloud represents either a threshold exceedance, triggering the alarm period, or a slight but not significant deterioration during an ongoing alarm period. The thunderstorm clouds signify a significant deterioration during the current alarm period, prompting the three-week alarm period to restart.

In an alert state, patients are required to complete the EWSQ-10P twice a week for three weeks and an orange shaded banner on the home screen reminds the patient of the alert status. The alert period lasts for a minimum of three weeks. Its extension depends on further deterioration of the patient’s condition. If the patient’s condition does not worsen further, the alert period automatically ends and patients resume completing the questionnaire weekly. The change in status can be seen by a shift in the weather icon from rain to sunshine. The wording and clarity of these icons were participatory reviewed and adjusted in focus groups during the preliminary study phase in collaboration with patient representatives to ensure their comprehensibility and effectiveness.

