**Fig. 4 Fig4:**
[figure not shown]
Overview of the digital clinic portal: Single patient status dashboard (overall risk of falling in relapse)

Clinicians are notified via email in four cases: A patient (1) enters the alert state, (2) extends the alert state, (3) exits the alert state or (4) missed a questionnaire twice in a row. The latter scenario is called “silent patient” and could constitute another early warning sign of relapse. In all cases, except for a patient exiting an alert period, the patient and clinician should promptly get in touch, e.g. via phone, to assess the patientˈ current (mental) health status. This is a shared responsibility of both, the patient and the clinician. As part of a shared decision-making process, the next treatment steps should be decided in a participatory manner. The action to be taken in response to an alert is not prescribed by the study and is left entirely to the shared decision-making between the clinician and the patient. For example, they may decide to provide psychoeducation, to improve sleep hygiene, issue a sick note, possibly adjust antipsychotic medication, or jointly deciding that no action is needed.

After the joint conversation about an (extended) alarm, clinicians must document the measures decided upon. This happens within the digital clinic portal, using a “Notes” function embedded in every patient profile. Additionally, a study team member will review the measures implemented in response to an alert at the next study visit.

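### With side-effect scales only at T0 and T12, the arm comparison describes side effects present at 12 months and cannot show those that arise and resolve earlier in the year

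*Protocol article*

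**What the plan says.** The Secondary outcomes section states the aim: "We evaluate the presence and severity of medication side effects using the Udvalg for kliniske undersøgelser scale (UKU-SERS", with ANTISIDES as the second scale. It then gives the timing: "Those two measures are assessed at baseline (T0) and after study completion (T12". Table 1 marks both scales as patient-rated at Visit 0 and Visit 4 only, so text and table agree. Under footnote f of Table 1, a patient who drops out has an early-termination visit modelled on the week-52 visit, which brings the final reading forward.

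Trial design gives the exposure period: "The intervention duration itself is 12 months". The section on the clinic portal for clinicians says of alerts that "The action to be taken in response to an alert is not prescribed by the study". Its examples of a response run from psychoeducation to "possibly adjust antipsychotic medication, or jointly deciding that no action is needed". The section on the app says of the alert state: "The alert period lasts for a minimum of three weeks".

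Most other measures in Table 1 are more frequent. PANSS-6, CGI, SOFAS, FORSE, EUROHIS-QOL, SDM-Q9, PAM-13, ZUF-8 and 15-STARS are taken at all five visits. Dated medication changes, alarms and the measures taken after them are recorded at T3, T6, T9 and T12.

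**The concern.** Medication adjustment is one of the routes by which the app is meant to work. The Introduction describes the predecessor system as enabling timely medication adjustments, and the portal section lists an antipsychotic adjustment among the possible responses to an alert. If the app arm has more adjustments than usual care, it may also have more side effects, at whatever point in the year the adjustments are made.

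The planned comparison has one post-baseline reading. It can show side effects present at week 52, or at early termination. It cannot show those that followed an adjustment in, say, month 4 and had gone by month 12. Symptoms, satisfaction and medication exposure are followed quarterly, while side effects are rated once after baseline. At stake is interpretation: similar scores at T12 could be read as showing that the app brought no excess of side effects over the year, which this schedule cannot establish.

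**Working it through.** The plan gives no figure on this point, so there is none to reproduce. The check asks what share of side-effect episodes a given schedule would see.

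**Inputs from the protocol article**
- Follow-up: 52 weeks (Trial design; Table 1).
- Current post-baseline reading: week 52 only (Secondary outcomes; Table 1).
- Visits already held: weeks 13, 26, 39 and 52, each with a window of 3 weeks either side (Table 1).

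**Assumptions, because the documents are silent**
- Onset of episodes is uniform over weeks 0 to 52.
- An episode lasts L weeks; values from 3 to 26 weeks are tried.
- The scale looks back R weeks; R = 0 and R = 4 give the range.
- Visits fall on their nominal dates.

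**Formulas.** An episode is seen at a visit in week v if it starts no later than v and ends no earlier than v − R. The start must therefore fall in a stretch of L + R weeks before the visit.
- T12 only: share seen = min(1, (L + R)/52).
- Quarterly: visits are 13 weeks apart, so share seen = min(1, 4(L + R)/52) = min(1, (L + R)/13).

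**Results**

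| Episode length L | T12 only, R = 0 to R = 4 | Quarterly, R = 0 to R = 4 |
|---|---|---|
| 3 weeks | 3/52 = 6% to 7/52 = 13% | 3/13 = 23% to 7/13 = 54% |
| 6 weeks | 6/52 = 12% to 10/52 = 19% | 6/13 = 46% to 10/13 = 77% |
| 13 weeks | 13/52 = 25% to 17/52 = 33% | 100% |
| 26 weeks | 26/52 = 50% to 30/52 = 58% | 100% |
| Persisting to T12 | 100% | 100% |

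**Where T12 alone misses more than half.** This needs (L + R)/52 < 0.5, that is L < 26 − R. The limit is 26 weeks with no look-back and 22 weeks with a 4-week look-back.

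**The case against.** The strongest reply is that nothing here is stated wrongly. The outcome is set for T0 and T12 in the text and in Table 1, and a randomised comparison of side-effect burden at 12 months is valid. Secondary outcomes are analysed as exploratory. Spacing some instruments more widely is an ordinary way to limit burden: Table 1 already lists eight patient-rated items for the app arm and nine for controls at T3 and T9, with WHODAS in addition at T6. All of this stands. The point is a limit on what the outcome can show, not an error.

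Four stronger readings are tempting, and the documents do not support them.

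- *Medication changes last about as long as the three-week alert.* Three weeks is the minimum length of the alert state with twice-weekly questionnaires. The response to an alert is left open and may be no action. No section says how long a medication change lasts or that it ends with the alert.
- *The schedule misses most treatment-related harm.* That holds only for side effects shorter than about 22 to 26 weeks. Their duration is not given, and persistent effects are all seen at T12.
- *Such side effects arise only in the app arm.* Control patients also change medication. The question is whether the app arm has an excess.
- *Side effects are otherwise untracked.* Medication side effects are a coded reason for drop-out, and about 20 end-of-study interviews in the intervention arm ask about potential side effects. For alerts, "a study team member will review the measures implemented in response to an alert at the next study visit". Adverse-event reporting may be in the full protocol, which is not shown. Still, the drop-out code covers only patients who leave, the interviews have no control comparison, and the review of measures records what was done. None of these gives a scale rating during the year in both arms.

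It can also be said that quarterly readings are no complete cure. For 3-week episodes they would still miss 46% to 77%. That is correct; the gain is clearest for episodes of about 6 to 13 weeks.

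**Conclusion.** The point holds as a design limitation of an exploratory secondary outcome. UKU-SERS and ANTISIDES at T0 and T12 compare the arms on side effects present at 12 months or at early termination. They cannot show side effects that follow an earlier medication adjustment, alert-triggered or not, and resolve before the final reading.

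For episodes of 6 to 13 weeks, T12 alone would see roughly 12% to 33%, against 46% to 100% with quarterly readings. These figures rest on uniform onset, a look-back of 0 to 4 weeks and assumed durations, none of which the documents supply. The primary outcome and the sample size are not affected.

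**What to change.** Give one of the two patient-rated scales, for example ANTISIDES, at T3, T6 and T9 as well, in both arms. Analyse it with the multilevel repeated-measures model that the quantitative analysis section already plans, and relate it descriptively to the dated medication changes in Table 1. This would also give ratings before drop-out for patients who leave after T3.

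The cost is one more questionnaire at three visits already held: modest extra patient burden, no new visit and no additional assessor. Using one scale rather than both limits the burden.

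If the schedule stays as it is, state in the plan and in the report that the side-effect comparison concerns side effects present at 12 months or at early termination, and draw no conclusion about side effects over the year from it. That costs nothing.

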#### Qualitative data

A qualitative approach complements the quantitative data collection, enhancing result validity and facilitating interpretation. Using a semi-structured interview guide, built upon previous clinical intervention studies conducted by our research group in this target population [47–49], questions regarding the feasibility, implementation, practicality, fear or relapse, potential side effects, and potential effects of the proposed digital intervention is addressed in single interviews with participants of the intervention group at the end of the study phase. We conduct approximately 20 interviews until content saturation is reached [50]. Additionally, we record sessions between clinicians and patients (i.e., approximately 20 patient-clinician dyads; until content saturation is reached) during the study period in both conditions, i.e., intervention and control group, to observe direct interactions during treatment, effects of the proposed intervention on shared-decision making, utilization of the digital intervention and potential differences in the groups in terms of conversation analysis.

### Data analysis

#### Analysis of quantitative data

The primary outcome parameter (psychiatric hospital admission) will be analyzed using a mixed model (logistic regression) with random intercepts for wards. Exploratory analyses of secondary outcome parameters will also be conducted: Differences in the time to hospitalization and simple relapses will be analyzed using a Kaplan-Meier curve and the log-rank test or within a generalized linear model framework (“Piecewise Exponential Model”). Additionally, we want to explore whether the effect of treatment is related with eHealth literacy and the acceptance of digital interventions with a subgroup analysis. Other secondary outcome parameters will be analyzed using mixed-effect regressions with random intercept for wards (logistic regressions if binary and linear regressions if continuous). If there are repeated measures available, this will be investigated within a multilevel framework, with random intercepts for subject and random slopes for time, if applicable.

Following the ITT principle, people that withdraw from the study (missing follow-up) need to be accounted for in the analysis. To deal with missingness, the primary analysis will adjust for baseline PANSS-6 score and age, since we expect these variables to be related to missingness. We expect an adjusted analysis to be the most efficient way to account for missing data in our experiment, mostly because of the binary outcome and the structure of missingness that is common in RCTs [51, 52]. The considerations for missing data will be subject to a sensitivity analysis. For this, missing values will be imputed with MICE (Multiple Imputation for Chained Equations) under a Missing at Random assumption. Imputation is an attractive alternative to our primary analysis, since there are many possible auxiliary variables measured at baseline that are not incorporated into the adjusted primary analysis. Additionally, in the case that there is a lot of dropout of similar structure (Reasons for Dropout), a sensitivity analysis under a MNAR assumption (pattern-mixture models) will be conducted.

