### Sample size and recruitment

We aim for a sample size of *N* = 110 patients recruited from *n* = 8 clinics. The sample size calculation is based on the outcome “number of patients requiring inpatient psychiatric admission within one year.” A randomized pilot study using a simple text message-based solution to monitor early warning signs showed large effect sizes [28]. Since we expect the pilot study effect to be inflated and cluster effects present in our study, we opt for a considerable smaller, but still moderate effect (w = 0.30) for sample size calculation. Using a chi-squared test without cluster effects, a group size of 44 patients per group provides a power of 80% to detect a population effect of w = 0.30 with a two-sided Type I error rate of 5%. Assuming a dropout rate of approximately 20% [28], 110 patients need to be recruited. An approximately equal distribution across the eight centers is planned.

Identification of suitable patients and recruitment is supported by local clinicians in the clinics. Flyers and posters at local study sites support the recruiting process. Additionally, patients are recruited at external centers, such as counseling centers, assisted living groups, or self-help groups. To ensure a comprehensive recruitment process, social media is also included. Experienced study staff at the lead center, Klinikum rechts der Isar in Munich, and the Berlin study center are responsible for enrolling participants in the study, including obtaining informed consent. External patients are getting affiliated with one of the participating clinics for the duration of the study. They can choose to fully transfer to our outpatient clinics during the study period or remain with their local doctor while simultaneously attending the participating outpatient clinic.

A study phone will be provided for patients who do not own a private smartphone but still possess basic digital skills, such as using a PC or tablet, and having an internet connection at home. However, these cases are reviewed individually and thoroughly to ensure that no bias arises.

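### Grouping the eHealth literacy and acceptance scores for the planned subgroup analysis would lose information that a treatment-by-score interaction keeps

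*Protocol article*

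**What the plan says.** In the protocol article, under Analysis of quantitative data, the moderator question is put in one sentence: "we want to explore whether the effect of treatment is related with eHealth literacy and the acceptance of digital interventions with a subgroup analysis". It follows the announcement that "Exploratory analyses of secondary outcome parameters will also be conducted". The sentence gives no cut-point, number of groups, interaction term or outcome.

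The two moderators are described under Baseline parameters: "Patients additionally provide answers to the German version of the eHeals questionnaires (eHeals-g) on health-related Internet use", and "we ask patients and clinicians about their acceptance of digital health interventions". Table 1 lists both at T0 only. It marks eHeals-g as patient-rated and the acceptance questionnaire as rated by both patient and clinician. The article does not say which acceptance rating is meant as the moderator.

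The primary outcome "will be analyzed using a mixed model (logistic regression) with random intercepts for wards", adjusted for baseline PANSS-6 and age. The sample size covers only the overall comparison of the two arms.

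**The concern.** Whether a treatment effect is related to a score is a question about a gradient. The method named to answer it works with groups. To form groups from a questionnaire score someone must choose a cut. Patients just either side of it are then treated as different, and patients far apart on the same side as alike. If effect modification is roughly linear, this lowers precision wherever the cut is placed, and the result also depends on that choice.

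The trial is small for any question of effect modification, so it has little precision to spare. A clear answer would be useful, because the authors hope to bring the app into routine care and would want to know whether its benefit depends on digital skills or attitudes. Only this exploratory question is at stake. The primary comparison is not.

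**Working it through.** **Inputs from the article (Sample size and recruitment).** w = 0.30, two-sided 5%, 44 evaluable patients per group (88 in total), 80% power, about 20% dropout, 110 recruited.

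**The article's own figure.** For a chi-squared test with 1 degree of freedom the noncentrality is N × w² = 88 × 0.09 = 7.92, which gives power 0.804. The normal approximation needs (1.960 + 0.842)² / 0.09 = 87.2 patients. With dropout, 88 / (1 − 0.20) = 110. The stated sample size reproduces. The article gives no figure for the subgroup analysis.

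**Assumptions for the rest (not in the article).** The score is normally distributed and the interaction is linear in it. The information kept after grouping is then the squared correlation between the score and its grouped version.

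- Two groups cut at quantile p, with c the normal quantile and φ the normal density: φ(c)² / (p(1 − p)).
- Median split: 0.3989² / 0.25 = 2/π = 0.637 kept, a loss of 36%.
- k equal groups: the between-group variance of the score.

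| Grouping | Kept | Lost |
|---|---|---|
| Quintiles | 0.897 | 10% |
| Quartiles | 0.861 | 14% |
| Tertiles | 0.793 | 21% |
| Median split | 0.637 | 36% |
| 60/40 | 0.622 | 38% |
| 70/30 | 0.576 | 42% |
| 80/20 | 0.490 | 51% |
| 90/10 | 0.342 | 66% |
| No grouping | 1 | 0% |

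The rows with three or more groups count information only. Spreading the test over several degrees of freedom would cost further power.

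**What a median split would mean.** In effective patients, 88 × 0.637 = 56 and 110 × 0.637 = 70. In power, a test with 80% on the continuous score falls to Φ(2.802 × √0.637 − 1.960) = Φ(0.276) = 61%. One with 50% falls to Φ(1.960 × √0.637 − 1.960) = Φ(−0.396) = 35%.

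**Illustration for a binary outcome.** 88 patients, 1:1 allocation, and assumed admission risks at the mean score of about 40% against 20%. The model was ordinary logistic regression with a Wald test and no ward effect, with 1,500 simulated trials per setting (1,476 to 1,496 usable).

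| Interaction, log-odds per SD | Power, continuous score | Power, median split |
|---|---|---|
| 0.5 | 15% | 9% |
| 0.8 | 31% | 16% |
| 1.2 | 56% | 30% |

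On the odds-ratio scale these interactions are e^0.5 = 1.6, e^0.8 = 2.2 and e^1.2 = 3.3 per SD. A separate simulation of 2,000 trials with likelihood-ratio tests, whose assumed risks are not recorded, gave 36% falling to 25% (0.8 per SD) and 61% falling to 43% (1.2 per SD). The levels depend on the assumed risks and on the test. The direction is the same throughout.

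**The case against.** The strongest reply is that the defect is inferred. The article does not say that the scores will be dichotomised. Asking whether the effect of treatment is related to a score already describes an interaction, and subgroup analysis is often a loose label for any study of effect modification, interaction tests included. The analysis is exploratory, and the coding of a moderator is a detail that a condensed article may leave to the full protocol or the analysis plan. The gain is also modest: at 0.5 log-odds per SD the comparison is 15% against 9%, so neither approach answers the question. Nor does grouping always lose. If the effect changed in a step at a known score, a cut at that value would serve well.

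Most of this stands, and it rules out three stronger readings that a reader might infer:

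- That the trial has chosen subgroups in place of an interaction. The article neither names nor excludes an interaction term.
- That a third of the information will be lost. This needs a median split of a normal score with a linear interaction, and the article states none of these.
- That each subgroup will be tested separately, so that the app is declared effective only in digitally literate patients. No within-subgroup tests are described. The hazard would be real if they were done. With 44 patients per half and w = 0.30 in both, the noncentrality is 44 × 0.09 = 3.96 and power is 51% per half, so exactly one half would be significant in 2 × 0.512 × 0.488 = 50% of trials with no true difference between halves.

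What the reply does not remove is that the article names a method, and taken at its word that method groups two questionnaire measures. The primary mixed logistic model in the same section could carry the scores ungrouped.

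**Conclusion.** The point holds as a minor, low-cost improvement to an exploratory analysis. It is not a demonstrated error. If the eHealth literacy and acceptance scores are cut into groups, information is lost: about 36% at a median split, and from about 10% (quintiles) to 66% (a 90/10 split) across the groupings examined. These figures assume a normal score and a linear interaction. If the authors already intend an interaction with the ungrouped score, the loss is nil and the change only clarifies the wording. Power is low under either approach unless the interaction is very large. The primary result and the sample size of 110 are unaffected.

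**What to change.** Replace the closing words of the sentence, which name a subgroup analysis, by:

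> by adding the continuous baseline score and a treatment-by-score interaction to the primary mixed logistic model, in a separate model for each score (eHeals-g; acceptance, stating whether the patient or the clinician rating is used).

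Report the interaction with its 95% confidence interval. Show the treatment effect at chosen percentiles of the score, for example the 25th and 75th, for display only. Draw no conclusions from within-subgroup p-values, and keep the analysis exploratory. The wording takes the primary outcome as the one meant. If another outcome is intended, the same two terms go into that outcome's model.

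The cost is one sentence in the protocol or analysis plan and no extra data. The downside is that linearity on the logit scale is assumed. A plot should check this.
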